### Primary efficacy endpoint

The primary efficacy outcome for this trial will be assessed by comparing the changes in vitamin D levels and inflammatory markers (IL-6, monocyte chemoattractant protein-1 (MCP-1), and C-reactive protein (CRP)) between two groups. The rate of mortality in TBI patients until 28 days after admission (in ICU and regular ward) will be assessed in high- and low-dose vitamin D supplement groups. The impact of high dose versus low dose of vitamin D will be analyzed, with and without adjustment for age, sex, type of brain injury, and severity of injury. If the results differ after adjusting for the variables, the results of both analyses will be reported.

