### Study objectives and rationale

The primary goal of the present study is to investigate the effect of daily intake of high-dose vitamin D (cholecalciferol) supplements (100,000 IU) versus low-dose vitamin D supplements (1000 IU) on mortality rate and inflammatory markers through a double-blind, randomized, controlled clinical trial on TBI patients. According to previous observational studies, TBI patients with vitamin D deficiency had higher mortality rate and neuroinflammation in comparison with TBI patients with vitamin D sufficiency [15, 17]. Also, as vitamin D deficiency is highly prevalent in critically ill patients, rapid normalization of this deficiency may be beneficial to these patients [7, 19, 20]. For this reason, we hypothesized that rapid correction of vitamin D deficiency in TBI patients may improve inflammation and decrease mortality rate. This study will also evaluate seven secondary outcomes that may be influenced by vitamin D administration in neurocritical patients. In order to determine the effects of high-dose vitamin D intervention, (1) Glasgow Coma Scale (GCS), (2) time of final weaning, (3) time of discharge from ICU, (4) SOFA (Sequential Organ Failure Assessment) score, (5) APACHE II (Acute Physiology and Chronic Health Evaluation II) score, (6) delirium severity, and (7) parathyroid hormone (PTH) test will be assessed in the treatment group compared to the control group. The study participants will be recruited from adult wards at trauma referral hospitals namely Kamyab and Taleghani in Mashhad, Iran. This study is a phase II RCT, and it has started from August 2019 and will carry on for 5 months.

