### Sample size

To calculate the sample size, in accordance with a previous study [7], interleukin 6 (IL-6) will be used as the main variable and the type 1 error is considered with an alpha of 0.05. We estimated 62 TBI patients with 80% power to detect an effect size of 0.5 for reduction of IL-6 between the intervention and control groups as calculated with the formula shown below. Considering 20% dropouts in this study, the total sample size is estimated to be 37 participants in each group as calculated in the below formula [7]:
$$ \frac{\left(Z1-\frac{\alpha }{2}+Z1-\beta \right)2\ \left(\delta 12+\delta 22\right)}{\left(\upmu 1-\upmu 2\right)2} $$

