### Proposed analysis

To determine the normal distribution of variables, the Kolmogorov-Smirnov test will be conducted. The analysis will be performed according to the intention-to-treat (ITT) test. We perfomed an independent t-test or the Mann-Whitney test for continuous variables and the chi-square or Fisher exact test for categorical variables. Repeated measure one-way analysis of variance (ANOVA) or multivariable covariance analysis (ANCOVA) will be conducted to examine differences in severity of brain injury score (GCS), APACHE II score, SOFA score, delirium score, and all variables at study baseline between the two groups. Kaplan-Meier test was conducted and compared with the use of the log-rank test for estimates of survival time. The *P* values less than 0.05 will be considered statistically significant.

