## Discussion

In the present study, if vitamin D significantly reduces the rate of mortality and inflammation in TBI patients, it can potentially provide the background for larger and well-designed multicenter clinical trial studies to establish the effect of vitamin D supplementation on TBI patients. Furthermore, vitamin D treatment is inexpensive and safe with minimal side effects and also could have positive impacts on critically ill patients (such as decreased mortality rate and hospital length) according to previous studies [7, 13, 14, 23, 24]. Potential limitations of the proposed study are as follows: measurement of vitamin D3 concentration with the chemiluminescence test instead of the gold standard method (liquid chromatography-tandem mass spectrometry). Another limitation is TBI patients’ blood transfusion because of trauma and bleeding; some TBI patients may require blood transfusion during the study, which may affect the biochemistry outcomes. Albumin injection in hypoalbuminemia patients can affect the levels of serum albumin. Also, TBI patients may need to undergo other surgeries than brain surgery; thus, this factor could affect the study outcomes. For this reason, we will compare mortality rate and inflammatory cytokine levels in all participants (intervention and control) and separate patients with anemia and hypoalbuminemia in each group. If the rate of death or inflammation in patients with anemia and hypoalbuminemia is different from those in the case or control group, the results will be reported separately. Based on recent studies, we have considered the suggested vitamin D dose (100,000 IU/day for 5 days) by Han et al. [23], as it is shown to be safe and efficacious in critically ill patients. Therefore, we believe that the present study could elaborate the necessity of vitamin D treatment and its efficacy on TBI patients at ICU.

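### Five measures are primary with no order or success rule, each tested at P<0.05, and one of them (serum vitamin D) shows delivery of the dose rather than efficacy

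*Protocol article*

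**What the plan says.** Four sections of the protocol article bear on what is primary, and the Discussion adds a fifth description.

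- **Primary efficacy endpoint.** "The primary efficacy outcome for this trial will be assessed by comparing the changes in vitamin D levels and inflammatory markers", the markers being IL-6, MCP-1 and CRP. The same section continues: "The rate of mortality in TBI patients until 28 days after admission (in ICU and regular ward) will be assessed". All of this is to be analysed with and without covariate adjustment.
- **Sample size.** "interleukin 6 (IL-6) will be used as the main variable", and "the type 1 error is considered with an alpha of 0.05". No other endpoint has a sample-size basis.
- **Study objectives and rationale.** The primary goal is the effect of high versus low dose "on mortality rate and inflammatory markers through a double-blind, randomized, controlled clinical trial on TBI patients". The serum vitamin D level is not part of that goal.
- **Proposed analysis.** The only decision rule is that P "values less than 0.05 will be considered statistically significant". Nothing splits or orders the alpha.
- **Discussion.** A larger trial would be justified "if vitamin D significantly reduces the rate of mortality and inflammation in TBI patients". The vitamin D level is absent here too.

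Study assessments puts the marker measurements at baseline and days 7 and 14. No day is named as primary.

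**The concern.** A reader of the final report needs to know which result decides the trial. The article names five, does not say whether one or all must succeed, and does not carry the IL-6 choice from the sizing section into the endpoint section. Three problems follow.

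1. If any one significant measure may be presented as a primary result, the type I error for the primary claim exceeds the 5% used in the sizing.
2. Serum vitamin D is counted as primary efficacy. The trial's hypothesis is that correcting the deficiency may improve inflammation and mortality, so the level is the means and not the benefit. A difference in it can be reported as a primary efficacy result while inflammation and mortality are unchanged.
3. The sections disagree. An analysis plan cannot follow all of them without choosing among them.

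**Working it through.** **Inputs from the article.** Five measures (Primary efficacy endpoint); alpha 0.05, two-sided because the formula uses Z at 1−α/2, 80% power, effect size 0.5, 62 patients before dropout and 37 per group after (Sample size); one P<0.05 threshold (Proposed analysis); 100,000 versus 1000 IU, 1:1 (Study design and setting); baseline level below 20 ng/ml (Inclusion criteria).

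**Assumed, not in the article.** The correlation between tests (0.3 to 0.7) and the standardised between-arm difference in serum vitamin D (0.8 to 1.0).

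**Step 1: the plan's own figure.** The article says: "We estimated 62 TBI patients with 80% power to detect an effect size of 0.5 for reduction of IL-6". With d = 0.5, n per group = 2 × ((1.960 + 0.842)/0.5)² = 62.8, so 63 per group or 126 in total. The stated 62 is close to the per-group result but is used as the total, that is, 31 per group. This matters here only because it sets the power that a single IL-6 primary endpoint would have (step 4).

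**Step 2: family-wise error for IL-6, MCP-1, CRP and mortality.** Serum vitamin D is left out because it is expected to differ.

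- Independent tests, 0.05 each: 1 − 0.95⁴ = 0.185.
- Equally correlated normal test statistics (simulated):

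| Common correlation | P(at least one P<0.05), all four null |
|---|---|
| 0 | 18.5% |
| 0.3 | 17.4% |
| 0.5 | 15.7% |
| 0.7 | 13.0% |

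Even at 0.7 this is 13.0/5 = 2.6 times the nominal level. These figures are two-sided. Counting only false results in favour of high dose, with independent tests, gives 1 − 0.975⁴ = 9.6% against a nominal 2.5%.

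**Step 3: power for serum vitamin D.** Two-sample t-test, two-sided 0.05, noncentrality d × √(n/2):

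| Assumed d | 31 per arm | 37 per arm |
|---|---|---|
| 0.8 | 87% | 92% |
| 1.0 | 97% | 99% |

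These do not depend on any effect on inflammation or mortality.

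**Step 4: IL-6 as the only primary endpoint.** The error is 5%. Power at d = 0.5 by the same t-test is 49% with 31 per arm and 56% with 37 per arm (50% and 58% by the normal approximation).

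**The case against.** **Success is described elsewhere.** The abstract's discussion ties a positive outcome to lower inflammatory cytokines, and the main Discussion to mortality and inflammation. If the latter is read as requiring both, the error is not inflated. This stands as a limit: the 18.5% applies only under an any-one-counts reading. The article does not state that reading, but does not exclude it either.

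**A partial ranking exists.** IL-6 is called the main variable. That is true, but only for sizing. The endpoint section does not single it out.

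**Multiplicity is often left to the analysis plan, and this is a condensed article of a phase II trial.** A missing correction procedure would not be a finding. The choice of primary measures, however, is made in this document, and it differs between sections.

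**Stronger readings that the document does not support.**
- A reader might infer that a positive primary result is close to guaranteed and says nothing about efficacy. That needs an any-one-wins rule and a large vitamin D effect, and the article states neither. The second half would be true of a win on vitamin D alone, not of one on IL-6 or mortality.
- A reader might count three markers at two days plus mortality as seven tests, giving 1 − 0.95⁷ = 30.2%. That assumes a separate test per day and independence. The same marker in the same patients is correlated across days, and the article lists repeated-measures ANOVA among its methods, so one test per marker is possible.
- A reader might add that mortality is underpowered. The article gives no event rates, so any such figure rests on assumed ones, and low power would not show that the endpoint definition is wrong.

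**Conclusion.** The point holds. The article places five measures under one primary heading without order or success rule, applies one 0.05 threshold, sizes on one of them, and includes a measure that its own primary goal leaves out.

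If one significant result is taken as primary success, the two-sided error for the four efficacy measures is 18.5% under independence and about 13% to 17% at assumed correlations of 0.7 to 0.3, more than twice 5% throughout.

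That serum vitamin D reflects delivery of the dose follows from the 100-fold dose contrast in deficient patients and from the trial's own hypothesis. That it would very probably be significant (87% to 99% power) rests on the assumed difference of 0.8 to 1.0.

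**What to change.** - Name IL-6 as the single primary endpoint, at one stated time point and with one stated analysis adjusted for baseline. The Sample size section already points to IL-6. The article does not favour day 7 or day 14, or a particular scale, so the sponsor must choose and give the reason.
- Make MCP-1, CRP, the other time point and 28-day mortality secondary, either under a stated multiplicity procedure or labelled exploratory. Report mortality as an estimate with its 95% confidence interval.
- Reclassify serum vitamin D as a treatment-delivery measure.
- Align Study objectives and rationale, Sample size, Primary efficacy endpoint and Discussion with this hierarchy.

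**Cost.** No new patients or measurements are needed, but it is more than a change of wording. Trial status says recruitment ended in December 2019, so the choice must be dated before unblinding or declared in the report as a change. Only IL-6 could then carry a primary claim, and at d = 0.5 its power is about 49% to 56% with 31 to 37 per arm. A non-significant result would therefore not show that there is no effect, and the report should say so.

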### Inclusion criteria

Patients: traumatic brain injury adults aged 18–65 years oldAdmission to neurocritical care unit with all type of TBI diagnosisGlasgow Coma scale 7–9TBI patients with vitamin D (25-hydroxy vitamin D3) levels lower than 20 ng/mlReceived informed consent from patient’s parents or family members prior to intervention

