### Non-entry criteria

Patients with hypercalcemia (Ca > 10.8 mg/dl)TBI patients who are NPO more than 48 h or have started total parenteral nutrition (TPN)Severe and active bleedingPatients treated with inotropic and corticosteroid drugsPatients treated with therapeutic dose of any vitamins and minerals apart from the routine ICU protocolPatients with body mass index (BMI) > 40 kg/m^2^ and BMI < 17 kg/m^2^History of any disease such as autoimmune disorders, cancer, sepsis, infection, liver disorder, kidney disorder, diabetes, heart failure, and metabolic diseasesKnown pregnancy and lactationPatients who are transferred from other ICUs after > 1 week

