### Secondary efficacy endpoints

All analyses will be conducted with and without adjustment for age, sex, type of brain injury, and severity of the injury. Time to event analysis will be analyzed similarly as the primary endpoint. The secondary outcomes are listed below:
Comparison of GCS score changes between the intervention and control groups during ICUComparison of APACHE II and SOFA scores between the intervention and control groups during ICUComparison of incidence of delirium between the intervention and control groups during ICUComparison of changes in PTH levels between the intervention and control groups during ICUComparison of time of discharge from ICU in patients treated with high-dose and low-dose vitamin D groups (during the first 28 days of admission)Comparison of time to weaning from mechanical respiratory support in patients treated with high-dose and low-dose vitamin D groups (during the first 28 days of admission)Comparison of need for a tracheostomy between the intervention and control groups during ICU stayComparison of occurrence of infections among the intervention and control groups during ICU stay

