### Trial status

This trial (protocol version number version 1.1, November 13, 2017) is ongoing. Participant recruitment began on August 11, 2019, and completed on December 21, 2019. The trial procedures are expected to be completed by the end of January 2020.

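### The 28-day windows for mortality, ICU discharge and weaning run from admission, not randomisation, so follow-up after randomisation is unequal and some post-treatment events are lost (minor)

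*Protocol article*

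**What the plan says.** Under Primary efficacy endpoint, the protocol article fixes the mortality window: "The rate of mortality in TBI patients until 28 days after admission (in ICU and regular ward) will be assessed". Under Secondary efficacy endpoints, time of ICU discharge and time to weaning from ventilation are each compared "during the first 28 days of admission", and the same section adds: "Time to event analysis will be analyzed similarly as the primary endpoint". Proposed analysis names the survival method but no starting point: "Kaplan-Meier test was conducted and compared with the use of the log-rank test for estimates of survival time".

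Several steps stand between admission and entry. Inclusion criteria require 25-hydroxy vitamin D below 20 ng/ml and "informed consent from patient’s parents or family members prior to intervention". Non-entry criteria bar "TBI patients who are NPO more than 48 h", so a shorter fasting period is compatible with entry. They bar patients from other ICUs only when the transfer comes after more than a week, so earlier transfers are eligible.

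Study assessments uses a second clock. It ties the baseline sample to ICU admission but counts days 7 and 14 from the intervention.

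**The concern.** A patient who dies before the vitamin D result, consent or allocation never enters the trial. Each participant's days between admission and randomisation are therefore survived by construction, yet an admission-based window uses them up as follow-up. Three things follow:

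- Patients who enter late are observed for less time after treatment starts, and deaths at the end of their 28 days from randomisation are not counted.
- If Kaplan-Meier curves start at admission, they include time in which that patient could not have an event. Survival looks slightly too high, and one risk set holds patients at different times since treatment.
- Times to discharge and weaning, if measured from admission, include days that the study drug could not have affected.

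Mortality is part of the stated primary goal and the trial has 74 patients, so deaths will be few and losing any is unwelcome. For transferred patients it is also unclear whether admission means the hospital, the first ICU or the study ICU.

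**Working it through.** The article gives no expected mortality, no share of transfers and no typical delay, so there is no figure of the plan's own to reproduce. The sample size rests on IL-6 and does not bear on this point. Mortality levels, hazard shapes and delays below are assumptions, except that the 7-day delay comes from the transfer limit in Non-entry criteria.

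**Follow-up after randomisation** = 28 − d, where d is the delay in days from admission to randomisation.

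- Admission means the study ICU, d assumed 0 to 2: 28 − 2 = 26, so 26 to 28 days.
- Admission means the first ICU, transfer at the limit, d = 7: 28 − 7 = 21 days. The share of the window spent before randomisation is 7/28 = 25%.

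**Recorded risk for a patient with delay d, constant hazard.** With m the mortality over 28 days from randomisation, λ = −ln(1 − m)/28 and recorded risk r = 1 − exp(−λ(28 − d)). For m = 0.25, λ = 0.2877/28 = 0.01027 per day.

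| m | d (days) | r |
|---|---|---|
| 25% | 2 | 23.4% |
| 25% | 3.5 | 22.3% |
| 25% | 7 | 19.4% |
| 15% | 7 | 11.5% |
| 35% | 7 | 27.6% |

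**Sensitivity to when deaths occur.** The share of that patient's expected deaths falling outside the window is (m − r)/m. The front-loaded case is a Weibull with shape 0.5: r = 1 − exp(ln(1 − m) × ((28 − d)/28)^0.5). For m from 20% to 40%:

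| d (days) | Constant hazard | Front-loaded deaths |
|---|---|---|
| 2 | 5.6 to 6.4% | 2.8 to 3.3% |
| 7 | 20.4 to 22.9% | 10.6 to 12.1% |

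**Cohort level.** A simulation used 37 patients per arm, 30% control mortality with constant hazard, and 3000 runs. Half the patients had a delay uniform on 0 to 7 days and the rest on 0 to 2 days. Early deaths were not excluded.

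| | From randomisation | From admission |
|---|---|---|
| Log-rank type I error | 5.7% | 5.8% |
| Mean deaths, no effect | 22.1 | 20.6 |
| Mean deaths, hazard ratio 0.4 | 16.1 | 15.0 |
| Power, hazard ratio 0.4 | 42% | 40% |

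Even with this generous mix of delays, the loss is about 1.5 deaths and 2 points of power.

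**The case against.** A reader might infer that the mortality comparison is biased. The documents do not support that. The delay is fixed before allocation, so it cannot differ systematically between arms, and the simulated type I error does not move. Death within 28 days of admission is also a definable endpoint. Its being lower than a different quantity is not in itself bias.

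A reader might also take it that follow-up in this trial ranges from 21 to 28 days. That needs admission to mean the first ICU. By linking the baseline sample to ICU admission, Study assessments points rather to the study ICU, which leaves mainly the wait for the test result and consent. The 19.4%, 11.5% and 27.6% figures describe a patient delayed by 7 days, not the cohort. Nor is there one stretch of time in which nobody could die; the event-free interval is each patient's own.

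The origin of the survival curves is an inference. Proposed analysis names none, and the wording for discharge and weaning could describe only an observation window. The full protocol may define time zero. Even so, the article itself fixes the mortality window from admission, and no outcome window for mortality, discharge or weaning is counted from randomisation. That part stands under either reading of admission.

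Finally, Exclusion criteria remove patients who die before 7 days, which takes out actual deaths and conflicts with the intention-to-treat analysis in Proposed analysis. This is a separate and larger source of death-free time, and changing the time origin does not cure it.

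**Conclusion.** The point holds as a minor one. Counting from admission makes follow-up after randomisation unequal and includes, for each participant, an interval that was event-free by design. The comparison between arms remains valid. The cost is a modest loss of post-treatment deaths, slightly overstated survival from admission, and pre-treatment days mixed into discharge and weaning times if these are measured from admission.

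For an individual with a 2-day delay the loss is small. With a 7-day delay it is roughly a tenth to a quarter of that patient's expected deaths, depending on how early deaths occur. The effect on the whole trial cannot be fixed from the article, because the share of transfers and the meaning of admission are not given.

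**What to change.** Define time zero as randomisation for 28-day mortality, the Kaplan-Meier and log-rank analysis, time to ICU discharge and time to weaning, with 28 days of follow-up for everyone. Report 28 days from admission as a descriptive figure only, and state which admission is meant for transferred patients. Fix the change before the allocation list is opened.

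The analysis itself needs only the randomisation dates. The added burden is vital status for a few more days, at most about 7, in late entrants. Because deaths are to be assessed "until 28 days after admission (in ICU and regular ward"), ascertainment may be in-hospital, so some of those days could require contact after discharge. The calendar allows it: recruitment ended on 21 December 2019, and a patient randomised that day reaches day 28 on 18 January 2020, while trial procedures are "expected to be completed by the end of January 2020".

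Separately, the exclusion of deaths before 7 days must be reconciled with the intention-to-treat analysis.
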